**Figure 2 F2:**
[figure not shown]
Study schema for the Tessa Jowell BRAIN MATRIX Platform study. GLH, Genomic Laboratory Hub; WGS, whole-genome sequencing.

The study aims to recruit 1000 patients within the UK over 5 years with participants followed up for up to 5 years. An initial 10 UK centres were opened to the TJBM study, as listed in online supplemental appendix 1, although further centre expansion is planned. The Standard Protocol Items: Recommendations for Intervention Trials (SPIRIT) checklist is provided as online supplemental appendix 2.^18^ The WHO Trial Registration Data Set is provided in online supplemental appendix 3.

10.1136/bmjopen-2022-067123.supp1Supplementary data

10.1136/bmjopen-2022-067123.supp2Supplementary data

10.1136/bmjopen-2022-067123.supp3Supplementary data

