### Consent

Online supplemental appendix 4 contains exemplar informed consent forms, with online supplemental appendix 5 the patient information sheets (PISs) and lay summary for the study. The investigator or an appropriately trained delegate must obtain written informed consent for each patient prior to performing any study-related procedure. Remote consent for platform entry is permitted by telephone or video consultation instead of face-to-face consultations.

10.1136/bmjopen-2022-067123.supp4Supplementary data

10.1136/bmjopen-2022-067123.supp5Supplementary data

In addition to consenting to join TJBM, patients will be required to provide agreement for:

The collection and analysis of biological samples (eg, tumour, blood), including access to existing and future samples.The collection of relevant clinical information, including imaging and pathology.The return of clinically relevant results back to the referring clinician.The use of, and sharing of, data for research, teaching, commercial and scientific purposes, including data sharing through The Brain Tumour Charity’s BRIAN (the Brain tumouR Information and Analysis Network) database.^19^
The collection of different aspects of health data from the NHS and other Department of Health organisations (in addition to medical records) for longitudinal analysis and follow-up.The use of clinical data to identify potential clinical trials or other research that they may benefit from.The sharing of samples for other ethically approved research projects.

In addition, and in line with GEL processes and studies such as the 100,000 Genomes Project, optional consent will be taken as to whether the patient would like to receive feedback about the evidence of inherited diseases (both underlying the cause of the cancer and non-cancer causes).

For centres submitting tumour tissue for WGS through the standard of care (SoC) NHS Genomic Medicine Service (GMS) pathway in England, an additional GEL consent step is currently required to confirm consent at the point of referral for the patient’s clinical indication. This additional GEL consent step is performed electronically or on paper and can be completed over the phone.

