### Statistical analysis plan

The target sample size for the study is 1000 patients. The primary remit of TJBM study is to establish a central data repository that will support the development and delivery of precision medicine for all patients with glioma in the UK. As such, there is no statistical basis behind the choice of target sample size, but this number will allow robust assessment of feasibility and subgroup analyses. Sample size for any clinical trials that are subsequently linked to the platform will be based on statistical justification.

A formal interim analysis of the primary outcome measure (TTMD) and any relevant secondaries will be performed after registration and diagnosis of the first 100 patients and after 500 patients. There are no formal stopping rules. Formal analyses of all study outcome measures will be performed once the study has completed recruitment (target 1000 patients) and completed the follow-up for all registered patients.

The analysis of TTMD will essentially be descriptive. The median TTMD will be reported overall and for each centre, together with the proportion of patients achieving TTMD within 28 days. Graphs of the change in both these summary statistics over time will be used to explore if TTMD changes during the course of the study. All estimates will be accompanied by 95% CIs. The time to completion of each node of tissue and imaging pathway will be reported as medians together with 95% CI, both overall and for each centre. Swimmer plots will be used to depict overall and node level timings for each patient.

For each type of tumour and biological sample, the proportion of sample passing QC and successfully undergoing WGS and EC will be reported with 95% CI and similarly for the imaging QC outcome measures. Inter-rater agreement of RANO will be assessed through Kendall’s coefficient of concordance.

Extent of surgical resection is evaluated from the postoperative MRI scan and is categorised as either closed biopsy, open biopsy, debulking <50%, subtotal resection 50%–90%, near total resection 90% to <100% or gross total resection 100%. The extent of surgical resection will be reported as the proportion falling into each category together with 95% CI.

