OS is defined as the time from date of diagnosis to the date of death with patients who are alive at the time of analysis censored at the date last seen in clinic. Intracranial PFS time is defined as the time from date of registration to the earliest of date of intracranial progressive disease or death from disease. The date of an event is defined as the earliest confirmation of progression by radiological assessment, clinical symptoms or multidisciplinary team (MDT). Patients without progression at the time of analysis will be censored at the date last seen in clinic.

OS and intracranial PFS will be analysed and plotted using the Kaplan-Meier method. Median times with corresponding 95% CI will be reported together with rates at 1, 2 and 5 years. Multivariable survival regression modelling will be used to explore prognostic factors, including, but not limited to, WHO 2021 classification, age, tumour volume, stage, methylation and mutation status.

Longitudinal measures of QoL will be generated from the QoL questionnaire according to the questionnaire-specific algorithms for scoring. The analysis of longitudinal QoL scores will essentially be descriptive. For each of the multiple QoL scores generated from the different questionnaires, the means, medians or proportions (as appropriate) will be plotted over time together with 95% CI. These repeated measures over time may be modelled, if appropriate, with a linear or more flexible mixed model that takes account of the within-subject correlation and will allow exploration of factors associated with the outcome.

Details of the type of intervention received and complications (eg, surgical wound infection) relating to SoC treatments received will be monitored and recorded throughout the follow-up period and reported descriptively as frequencies and associated percentages. In relation to initial local logical diagnosis, local pathological diagnosis and integrated histological–molecular diagnosis, any difference between the tiers of diagnoses will be highlighted and categorised as discordant, agreed, refined and reported descriptively as frequencies and associated percentages.

Confirmation of central storage of images and material, relevant targetable mutations identified by WGS and EC, and receipt of postmortem consent forms with confirmed central storage of samples will be recorded and reported descriptively.

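### Overall survival censors living patients at the last clinic visit but sets no matching limit on deaths, which can bias the promised 5-year rate downwards

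*Protocol article*

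**What the plan says.** The OS rules are in the Protocol article under Statistical analysis plan. The event is dated without reference to clinic attendance: "OS is defined as the time from date of diagnosis to the date of death". The censoring rule does refer to it: "patients who are alive at the time of analysis censored at the date last seen in clinic". The estimator and the reported quantities follow: "OS and intracranial PFS will be analysed and plotted using the Kaplan-Meier method", and "Median times with corresponding 95% CI will be reported together with rates at 1, 2 and 5 years".

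Three other statements bear on the point:

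- Study design: "participants followed up for up to 5 years". The 5-year rate therefore sits at the edge of the observation window.
- Statistical analysis plan: the final analysis waits until the study has "completed the follow-up for all registered patients". Interim analyses after 100 and 500 patients cover the primary outcome and whichever secondary outcomes are judged relevant.
- Consent: patients agree to "The collection of different aspects of health data from the NHS and other Department of Health organisations", for follow-up among other uses.

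The article does not give the clinic visit interval, the source of death dates, or whether clinic contact continues past 5 years. The schedule of events is in supplemental appendix 6, which is not shown.

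**The concern.** Kaplan-Meier estimation needs censoring to be unrelated to outcome. Take two patients last seen on the same day. One dies before the data cut-off and the other does not. If the death becomes known, the first stays in the risk set until death and counts as an event, while the second is removed at the last visit. Between the last visit and the cut-off the risk set keeps all the deaths and loses the survivors, so the estimated hazard is too high.

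The mechanism needs deaths to be found without a clinic visit. Besides the NHS-data consent, the article mentions sampling in the palliative phase, post-mortem tissue collection, and an adverse-event reporting period that runs to death. Each makes it plausible that deaths are learned of other than in clinic.

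At stake is a named secondary outcome, and in particular the 5-year rate, from a repository meant to support later trials.

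**Working it through.** The article states no OS estimate, event count or power, and says that the target of 1000 has no statistical basis. There is no figure to reproduce, so the check asks how large the bias could be under stated assumptions.

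**Assumptions (not in the article).** Exponential survival with median 120 or 40 months; visits every w months with random phase; all deaths to month 60 known; follow-up cut at month 60; curve read at month 59.9.

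**Formula.** Let h = ln 2 / median, and let v be the months left to month 60, within the last visit interval (v ≤ w).

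- Survivors still at risk: about S(60)·v/w, those whose last visit is still to come.
- Patients at risk who will die before month 60: about S(60)·h·v.
- Deaths occur at rate about S(60)·h.

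The apparent hazard is h / [v(1/w + h)] = k/v, with k = hw/(1 + hw). Integrating v from 0.1 to w gives

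KM(59.9) ≈ S(60 − w) · exp[−k · ln(w/0.1)].

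Example, median 120 and w = 6: S(54) = 2^(−54/120) = 0.7320; hw = 0.0347; k = 0.0347/1.0347 = 0.0335; ln 60 = 4.094. KM = 0.7320 × exp(−0.1372) = 0.6382, against a true 2^(−59.9/120) = 0.7075.

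| Median | w | S(60 − w) | k | ln(w/0.1) | KM(59.9) | True | Points | Simulated KM |
|---|---|---|---|---|---|---|---|---|
| 120 | 3 | 0.7195 | 0.0170 | 3.401 | 0.679 | 0.7075 | −2.9 | 67.6–67.9% |
| 120 | 6 | 0.7320 | 0.0335 | 4.094 | 0.638 | 0.7075 | −6.9 | 63.3–63.8% |
| 40 | 3 | 0.3724 | 0.0494 | 3.401 | 0.315 | 0.3542 | −3.9 | 31.2–31.5% |
| 40 | 6 | 0.3923 | 0.0942 | 4.094 | 0.267 | 0.3542 | −8.7 | 26.6–26.9% |

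Formula and simulation agree: about 3 to 4 points for 3-monthly visits and 7 to 9 points for 6-monthly.

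**Sensitivity to the reading point.** The term ln(w/v) grows without limit as v approaches 0. Reading the first 6-monthly case at month 59.99 gives 0.7320 × exp(−0.0335 × 6.397) = 0.591. A simulation with half the patients at median 13 months and half at 120, read at exactly month 60, gave −5.7, −10.8 and −22.3 points for 3-, 6- and 12-month gaps. At that point the risk set is nearly empty and the result depends on the number of patients simulated, so I do not use these as sizes.

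**When the bias goes away** (5-year rate):

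- All survivors seen at month 60: 0.0 points.
- 6-monthly visits, cut-off at month 63: about 0.6 points or less; at month 66: about zero.
- Clinic contact to study month 120: 0.0 to −0.1 points.
- Follow-up running past month 60, but 10% stop attending and their deaths are still found: about 1 to 2 points.

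**Earlier rates, final analysis.** The 1- and 2-year rates are off by 0.0 points, or at most about 0.8 if 10–20% leave clinic.

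**Interim at 500 patients.** Even accrual puts this at 500/1000 × 60 = month 30. In the half-and-half population above, the 1-/2-year biases are −1.6/−3.2 points (3-month gap), −3.2/−7.1 (6-month) and −6.7/−16.6 (12-month). The 5-year rate is not estimable then.

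**With a common cut-off.** Censoring every living patient at the date to which deaths are complete gives 0.0 points at 1, 2 and 5 years at the final analysis.

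**The case against.** The strongest reply is that the premise and the edge condition are both assumed. The article nowhere says that death dates come from record linkage, and it describes data entered by sites on case report forms. The visit schedule is not shown and may include a 5-year visit. If survivors are seen then, or contact continues for one more visit interval, the bias all but disappears. This stands: the size is conditional, and zero is among the possible values.

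A reader might infer that OS as a whole will be under-reported. The article does not support that. The final analysis waits for completed follow-up, so the 1- and 2-year rates, and medians reached before the last visit interval, are essentially untouched. The net direction is also open. OS runs from diagnosis, yet patients biopsied before the study's launch may join, and without allowance for delayed entry this pulls OS upwards. With an assumed 10–30% of such patients entering 12–60 months after diagnosis, the net 5-year bias was +1.5 to +10.6 points even under the clinic-visit rule. That is a separate issue of unknown size. It cannot be relied on to cancel this one.

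A reader might also infer that centres with fewer visits will look worse. No OS comparison by centre is planned: centre-level reporting is for diagnostic and pathway times. Nor is OS named as an interim outcome, so the interim risk arises only if it is judged relevant.

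It could be said that the source of vital status belongs in the analysis plan. But the article fixes the censoring date itself, so the point concerns a stated rule and not a missing detail.

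**Conclusion.** The point holds as a conditional weakness. The mechanism, and the downward direction of this rule taken alone, are sound if deaths are found outside clinic contact. The article permits that but does not state it. At the final analysis the exposure is mainly the 5-year rate. Of the cases worked, the material ones need follow-up cut at about month 60 with survivors not seen at that point; continued follow-up with some patients leaving clinic costs only a point or two. The 1- and 2-year rates are at risk only at an interim analysis that includes OS. All sizes rest on assumed visit gaps, survival curves and complete capture of deaths, and none should be read as a forecast of the reported result. The article does not guarantee the conditions that would make the rule harmless, and a common cut-off removes the dependence on them.

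**What to change.** Replace the OS censoring rule under Statistical analysis plan so that deaths and survivors share one source and one cut-off. Censor living patients at the date to which vital status is complete, for example the record-linkage or data cut-off date, capped at the follow-up limit. Do not count deaths after that date.

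Where no complete source exists, use the date last known alive and add a sensitivity analysis with a common cut-off. The date last known alive is not enough by itself, because it still precedes the cut-off for survivors while deaths count up to it.

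The cost is a change of wording and a vital-status check or extract. Whether the existing consent covers that extract should be confirmed first, since the consent text does not mention death registration.

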### Patient selection

Patients aged ≥16 years with newly diagnosed suspected WHO Grade II–IV glioma (as evidenced radiologically) suitable for a diagnostic or therapeutic surgical procedure resulting in a tumour sample matched to a blood sample or with progression with known WHO Grade II–IV glioma will be eligible.

Patients with primary spinal cord tumours, who are receiving active treatment of other malignancy, have contraindications to MRI and/or without standard of care imaging available, will be excluded.

Newly diagnosed patients with suspected WHO Grade II–IV glioma who are subsequently found to have a WHO Grade I tumour or non-brain tumour are expected to be a rare occurrence. If this event occurs:

If it is confirmed as a Grade I tumour, then the patient will remain eligible for the study and will continue to be followed up in accordance with the protocol.If it is confirmed as a non-brain tumour, then the patient will not remain on the study and no further follow-up data will be collected.

All patients must be able to provide written informed consent for the study.

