Planned subgroup analyses of outcome measures include the following: IDH mutated and wild-type tumours; residual enhancing disease (none, operable, inoperable); methylated and unmethylated tumours; age groups; types of diagnosis (WHO 2021 criteria only, epigenetic classification only, WGS analysis only, integrated diagnosis comprising all three); performance status; sex; biomarkers that emerge during the study (either discovered in the TJBM study or reported in the literature) that are deemed relevant after review by the Scientific Advisory Board (SAB).

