## Discussion

### Justification for patient population

The main aim of the TJBM study is to test the hypothesis that comprehensive genomic and epigenomic profiling of gliomas is feasible in a timely manner in the UK, and that the results improve stratification of patients for next-generation (targeted) therapies, ultimately improving outcomes and QoL.

Gliomas occur at all ages and their specific subtype is difficult to predict preoperatively. Therefore, the patient population eligible for the TJBM study is broad. It includes any patient who on preoperative assessment is suspected to have a diffuse glioma, or where a diffuse glioma remains a credible differential diagnosis, as established by the MDT at the recruiting site.

Recruitment is also open to patients with diffuse or atypical gliomas who had a biopsy before the launch of the TJBM study. This approach ensures that:

Patients with slow-growing diffuse gliomas that evolve over many years (oligodendrogliomas) may benefit from one or more of the clinical trials developed as part of the TJBM study and sample collection at tumour progression.Patients who potentially benefit most from comprehensive molecular diagnostics are not missed, which often are those with rare or atypical variants of glioma based on current diagnostics.^34^

The infrastructure for children with brain tumours in the UK is different to that of adults with epigenomic classification regularly used and with WGS shortly to be made available for all children with cancer. Thus, the challenges and opportunities are different for paediatric patients. Nevertheless, it is intended that children will be included within the TJBM study wherever appropriate. The recruitment of children and adolescents into the TJBM study will be coordinated with the UK’s paediatric oncology expert group(s).

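### One PFS definition from registration covers both newly diagnosed patients and patients who enter at progression, so the overall PFS figures depend on the entry mix

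*Protocol article*

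**What the plan says.** Under Patient selection, the protocol article opens the study to newly diagnosed patients with suspected Grade II–IV glioma who are suitable for surgery, and also to patients with known disease: "or with progression with known WHO Grade II–IV glioma will be eligible". The second route is deliberate. Justification for patient population states: "Recruitment is also open to patients with diffuse or atypical gliomas who had a biopsy before the launch of the TJBM study".

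The Statistical analysis plan section then gives a single PFS definition for everyone: "Intracranial PFS time is defined as the time from date of registration to the earliest of date of intracranial progressive disease or death from disease". Events are dated by this rule: "The date of an event is defined as the earliest confirmation of progression by radiological assessment, clinical symptoms or multidisciplinary team (MDT". The censoring rule is: "Patients without progression at the time of analysis will be censored at the date last seen in clinic". PFS is to be analysed by Kaplan-Meier, with the median and the rates at 1, 2 and 5 years, and prognostic factors are to be explored by multivariable regression.

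The subgroup list begins "Planned subgroup analyses of outcome measures include the following: IDH mutated and wild-type tumours". It goes on to residual enhancing disease, methylation, age, type of diagnosis, performance status, sex and emerging biomarkers. Entry route is not on it, nor among the named prognostic factors. Separately, Imaging data allows a progression to be backdated once later imaging confirms it, and states no lower limit at registration.

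**The concern.** Progression is both a way into the study and the event that ends PFS, and the text does not say how the two are kept apart. A patient who enters at progression already has a confirmed progression on record at registration. Nothing requires the PFS event to be a new one, and the censoring rule speaks only of patients without progression.

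Even if the qualifying progression is set aside, the two groups are at different points in their disease. For a new patient the event is usually the first progression after diagnosis; for a progression entrant it is a second or later one. A single curve mixes the two in whatever proportion happened to be recruited.

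At stake is what the PFS result describes. The platform is meant to support trials, and those trials are likely to address either newly diagnosed or recurrent glioma. An overall median that moves with recruitment mix is a poor description of either.

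**Working it through.** The plan states no PFS rate, no expected entry mix and no statistical basis for the target of 1000, so there is no figure to reproduce. The check is a reading of the passages together, followed by an illustration.

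**Passages side by side**

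- Entry (Patient selection): newly diagnosed, or "with progression with known WHO Grade II–IV glioma will be eligible".
- Origin and event (Statistical analysis plan): "Intracranial PFS time is defined as the time from date of registration to the earliest of date of intracranial progressive disease", or death from disease. No word such as new, or first after registration, limits the event.
- Date: the earliest of three sources, with no lower bound at registration.
- Split by entry route: none stated for the Kaplan-Meier analysis and none in the subgroup list. The prognostic factor list is open-ended but does not name it.

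Two readings are possible for a progression entrant. They are alternatives and cannot both apply to the same patient.

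- *Reading A, literal:* the earliest confirmed progression is the qualifying one, so PFS time is zero or less.
- *Reading B, forward from registration:* only a later progression counts. Times are positive, but first and later progressions are pooled.

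**Illustration**

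Assumptions, none of them from the documents: exponential PFS; a share f entering at progression, taken from 10% to 50%; and, for Reading B, a hazard ratio h of progression entrants to newly diagnosed patients of 1.5, 2, 3 or 6. Time is in units of the newly diagnosed median.

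Reading A: the curve starts at 1 − f, and the median ratio is 1 + log2(1 − f). For f = 30% this is 1 + log2(0.70) = 0.49.

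Reading B: solve (1 − f)·2^(−t) + f·2^(−h·t) = 0.5 for t. Check at f = 30%, h = 2, t = 0.802: 0.70 × 2^(−0.802) + 0.30 × 2^(−1.604) = 0.401 + 0.099 = 0.500.

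Overall median as a fraction of the newly diagnosed median:

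| f | A | B, h = 1.5 | B, h = 2 | B, h = 3 | B, h = 6 |
|---|---|---|---|---|---|
| 10% | 0.85 | 0.96 | 0.93 | 0.89 | 0.86 |
| 20% | 0.68 | 0.92 | 0.86 | 0.79 | 0.71 |
| 30% | 0.49 | 0.88 | 0.80 | 0.70 | 0.57 |
| 40% | 0.26 | 0.85 | 0.75 | 0.62 | 0.45 |
| 50% | 0 | 0.81 | 0.69 | 0.55 | 0.36 |

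The column h = 6 corresponds, for example, to assumed medians of 24 and 4 months (24/4 = 6) and is a steep case. In every column the overall median changes with f although PFS within each group is held fixed.

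**The case against.** A reader might infer that every progression entrant meets the endpoint at or before time zero. The documents do not establish that. A time from registration to an event runs forward, and the earliest confirmation is most naturally a rule for choosing among radiology, symptoms and MDT when dating one event, not for choosing among all progressions in a patient's history. An analysis with a whole entry group at zero or below is unlikely to be intended. So column A shows what the wording fails to rule out; it is not a forecast.

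The other side has further points:

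- The prognostic factor list is explicitly not exhaustive, so entry route could be modelled. This stands, but a covariate in a regression does not repair a pooled median or pooled yearly rates.
- The article condenses a fuller protocol, and details such as the entry baseline scan may be set out there. That is fair for the scan. But the article itself fixes the origin, event, dating rule, censoring and subgroups, and the concern is that these, as stated, do not suit the stated population.
- An overall PFS across Grades II–IV is already a mix, and users of patient-level data can select by entry route. Both are true and limit the harm. They do not make the planned summary easier to interpret.
- PFS is one of many secondary outcomes, there are no formal stopping rules, and linked trials will have their own sample size justification. This stands and limits the importance of the point.

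**Conclusion.** The concern holds as a pooling problem with a loosely worded event. Following the stated plan, the overall PFS median and the 1-, 2- and 5-year rates depend on the proportion who enter at progression, whichever reading is used. On the more natural reading, and with an assumed 30% share, the overall median is about 0.88 to 0.70 of the newly diagnosed median at hazard ratios of 1.5 to 3, and 0.57 at 6. These sizes rest on exponential curves and on assumed shares and hazard ratios. If few patients enter at progression, or their PFS is close to that of new patients, the effect is small.

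The stronger statement, that progression entrants will be scored at zero or less, is only one literal reading and is not part of this conclusion. The primary outcome, time to integrated diagnosis, is not affected by this point. The change should be made, but it does not threaten the study's main result.

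**What to change.** - Define the PFS event as the first intracranial progression confirmed after registration (or death from disease, as now), judged against imaging at entry. State that the qualifying progression is not an event and that no progression is backdated to before registration.
- Report the PFS median and the 1-, 2- and 5-year rates separately for newly diagnosed and progression-entry patients. A pooled curve may be shown as secondary.
- Add entry route to the planned subgroups and to the named factors in the prognostic model.

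The cost is a change of wording. Entry route is known from eligibility, so no new data are needed for the split. The downside is two smaller groups with wider confidence intervals, most noticeably for progression entrants if they are few.

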## Introduction

Gliomas are the most common primary tumour of the central nervous system (CNS), with an estimated annual incidence of 6.6 per 100 000 individuals in the USA,^1^ which is predicted to rise to 22/100 000 by 2035.^2^ In 2016, there were 5250 deaths from brain tumours in the UK, that is, 14 deaths per day.^2^ Malignant CNS tumours hold the poorest prognosis and are responsible for the highest estimated number of years of potential life lost (mean 20 years) among all cancers,^3^ and survival trends have remained generally static in comparison with other cancers.^4^

Gliomas have traditionally been divided into low-grade glioma (LGG; WHO I–II) and high-grade glioma (HGG; WHO III–IV) based on integrated classic histological features and molecular biomarkers.^5^ LGGs have an indolent course with patients commonly surviving a decade after diagnosis.^6^ However, the natural history of many WHO Grade II LGGs is progression to HGG. Approximately half of all newly diagnosed gliomas are classified as glioblastoma (GB; WHO IV), the most malignant type of brain cancer. Currently, the GB annual incidence is 3.2 per 100 000 population in the USA. This tumour occurs more frequently with advancing age; ranging from 0.4 per 100 000 population aged 20–34 years to over 15 per 100 000 population aged 75–84 years.^1^ It is widely recognised that elderly populations are rapidly increasing globally and this will have a significant impact on the burden of GB disease. Despite this, most studies still focus on patients younger than 65 years.

The current gold-standard treatment for newly diagnosed GB is surgical gross total resection, followed by radiotherapy with concomitant and adjuvant temozolomide. The aim of treatment is to delay tumour progression and extend overall survival.^7^ Despite decades of refinement, this approach results in a median survival time of only 12–14 months.

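### In long-survival groups, any median OS beyond 5 years from diagnosis would rest only on previously diagnosed entrants

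*Protocol article*

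**What the plan says.** All places are in the protocol article.

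- **Time origin and censoring (Statistical analysis plan).** "OS is defined as the time from date of diagnosis to the date of death". Survivors are censored at their last clinic visit.
- **Summary (Statistical analysis plan).** OS and intracranial progression-free survival (PFS) are analysed by Kaplan-Meier. "Median times with corresponding 95% CI will be reported together with rates at 1, 2 and 5 years". The sentence sets no condition on the median being reached and names no group.
- **Length of follow-up (Study design, text after Figure 2).** Recruitment runs over 5 years, "with participants followed up for up to 5 years".
- **Timing of the final analysis (Statistical analysis plan).** It takes place "once the study has completed recruitment (target 1000 patients) and completed the follow-up for all registered patients".
- **Who may enter.** Patient selection admits newly diagnosed suspected glioma "or with progression with known WHO Grade II–IV glioma will be eligible". Justification for patient population also opens recruitment to patients biopsied before the study was launched.
- **Expected survival (Introduction).** "LGGs have an indolent course with patients commonly surviving a decade after diagnosis". For glioblastoma it gives a median of 12–14 months and a share of about half of new gliomas.
- **Subgroups (Statistical analysis plan).** The list for the outcome measures begins with "IDH mutated and wild-type tumours". Low grade is not listed as a subgroup.

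**The concern.** The follow-up limit applies to each participant, and the final analysis waits for follow-up to finish, so staggered recruitment does not lengthen it. A newly diagnosed patient registers close to diagnosis and so contributes nothing beyond about 5 years on a time-from-diagnosis scale. A patient diagnosed years before registration contributes only at later times on that scale.

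If both kinds share one curve, the part beyond about 5 years is drawn entirely from the second kind. In a group where more than half are alive at 5 years, the median falls in that part. An unreached median would at least be visible as such. Here the curve continues, and a definite number can appear that describes patients selected for having survived to registration and, on the Patient selection route, for having progressed. A reader would take it as the survival of newly diagnosed patients in that group. The OS text does not say how delayed entry is handled.

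**Working it through.** The article states no OS figure or event count to reproduce, and it says that the target of 1000 has no statistical basis. The check therefore asks what the stated rules would produce.

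**Step 1. Newly diagnosed patients only.**
Inputs: 5 years of follow-up (Study design); a true median of m years. Reading the Introduction's remark on low-grade survival as m = 10 is an assumption, so m is varied. Exponential survival and no loss to follow-up are also assumed.

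Survival at 5 years: S(5) = 0.5^(5/m). For m = 10, S(5) = 0.5^0.5 = 0.707, so 29.3% die by 5 years.
- n = 300: 300 × 0.293 = 88 deaths, against 150 needed for the median.
- n = 500: 500 × 0.293 = 146 deaths, against 250 needed.

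Exact binomial probability that at least half of n die within 5 years:

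| m (years) | S(5) | n = 50 | n = 100 | n = 200 | n = 300 |
|---|---|---|---|---|---|
| 6 | 0.561 | 0.232 | 0.129 | 0.047 | 0.019 |
| 7 | 0.610 | 0.076 | 0.017 | 0.0011 | <0.0001 |
| 8 | 0.648 | 0.022 | 0.0016 | <0.0001 | <0.0001 |
| 10 | 0.707 | 0.0016 | <0.0001 | <0.0001 | <0.0001 |
| 12 | 0.749 | 0.0001 | <0.0001 | <0.0001 | <0.0001 |

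With a hazard that rises over time (Weibull shape 1.5), S(5) at m = 10 is 0.783 and the probabilities are smaller still.

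**Step 2. Adding previously diagnosed entrants.**
The article gives neither their share nor their time from diagnosis to registration, so both are assumed. The true OS median is 10 years throughout, and each patient is followed for 5 years from registration.

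*Model A: entry unrelated to prognosis.* Time from diagnosis to registration uniform over 0–15 years among those still alive; n = 200; exponential survival; 200 runs per setting.

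| Previously diagnosed | Entry time ignored: median reached; typical value | Delayed-entry risk sets: median reached; typical value; upper 95% limit reached |
|---|---|---|
| 0% | 0%; none | 0%; none; 0% |
| 20% | 82%; 14.1 years | 97%; 10.0 years; 68% |
| 50% | 85%; 15.8 years | 100%; 10.0 years; 91% |

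*Model B: entry at progression.* Median time to progression 4, 5 or 6 years, with the post-progression hazard set so that the OS median is 10 years; n = 450; 100 runs per setting.
- No progression entrants: a median in 0% of runs.
- 10–30% progression entrants: a median in 100% of runs. Typical values are about 10.7–11.3 years with entry time ignored and about 6.4–8.0 years with delayed-entry risk sets.

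Delayed-entry risk sets recover the truth under Model A. Under Model B they do not, because beyond 5 years everyone at risk has already progressed and has a higher hazard than the group as a whole.

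**Step 3. Whole cohort.**
Solve w × 0.5^(t/g) + (1 − w) × 0.5^(t/10) = 0.5, where w is the glioblastoma share, g its median in years (12–14 months), and 10 years is assumed for everyone else.
- w = 0.5: t = 2.6–2.9 years.
- w = 0.4: t = 3.6–3.9 years.
- w = 0.3: t = 5.1–5.2 years.

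At the Introduction's share of about half, the overall median falls well inside 5 years.

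**Step 4. What remains estimable.**
The 5-year rate (0.707 at m = 10) lies within the follow-up of newly diagnosed patients. So does the restricted mean to 5 years: (1 − 0.707)/(ln 2/10) = 0.293/0.0693 = 4.23 years.

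**The case against.** The strongest reply is that an unreached median is an ordinary Kaplan-Meier result, and that the same sentence already plans 1-, 2- and 5-year rates, which can be estimated. How to report an unreached median is commonly left to a statistical analysis plan, which is not at hand. This stands: an unreached median alone would be no finding. It does not answer the case in which a median is printed from patients who all entered after diagnosis. That case follows from the time origin, follow-up limit and eligibility that the article itself fixes.

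A reader might infer that the article promises a median for every group, or that it puts IDH-mutated survival at 10 years. It does neither. A median by IDH status is a fair inference from the survival and subgroup paragraphs read together, but it is not stated. The decade remark is qualitative and concerns low-grade glioma; no survival figure for IDH-mutated tumours is given.

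A reader might also infer that every previously diagnosed entrant has progressed, so that delayed-entry methods must fail. Patient selection ties this route to progression, but the wording on patients biopsied before launch is looser. Models A and B show that the size and direction of the error depend on this.

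Finally, OS is a descriptive secondary outcome with no test attached, which limits the consequence.

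**Conclusion.** The point holds for OS in long-survival groups. With at most 5 years of follow-up and a true median of 7–12 years, the chance that newly diagnosed patients alone reach the median is about 0.1% or less with 200 or more patients, and at most 8% with 50. If the true median were 6 years, that chance would be 5% with 200 patients and 23% with 50, so the point weakens as survival shortens. A median beyond 5 years would rest only on previously diagnosed entrants. With a true value of 10 years, the typical printed figure ranged from about 6.4 to 15.8 years over the assumed entry patterns and the two ways of treating entry time.

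These sizes rest on assumed survival curves, entrant shares and entry times, and applying them to IDH-mutated tumours is a further assumption. Overall and glioblastoma medians are not affected in this way, unless glioblastoma makes up only about 30% of the cohort, when the overall median reaches the 5-year edge. It would be too strong to extend the criticism to intracranial PFS: it runs from registration, and no failure is shown for it. It would also be too strong to call the OS analysis as a whole invalid.

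**What to change.** In the survival paragraphs of the Statistical analysis plan:

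1. Estimate OS from diagnosis in patients newly diagnosed at entry, and report OS in previously diagnosed entrants separately, timed from registration.
2. Quote an OS median with its CI only where the curve crosses 50% within the 5 years that newly diagnosed patients are followed.
3. Elsewhere rely on the planned 1-, 2- and 5-year rates. A 5-year restricted mean with 95% CI may be added; it is an option, not a necessity.

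This takes a few sentences and no new data. The costs are that some subgroups will show no median, and that the from-diagnosis analysis uses fewer patients.
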